### Economic evaluation

We perform two economic evaluation analyses (see below). The first is a cost-effectiveness analysis (CEA) to determine whether PPEP4All (compared to CAU) is favorably cost-effective at 1-year follow-up. The second is a budget impact analysis (BIA). The economic evaluation is based on the TiC-P questionnaire (see Fig. 2). The TiC-P questionnaire assesses healthcare utilization such as general practitioner (GP) visits and non-healthcare use such as absence from work, reduced efficiency at work, difficulties with job performance (absenteeism from paid work), and production losses without absenteeism from paid work (e.g., presenteeism). Using the area-under-the-curve method for the utility scores results in QALY outcome per patient.

#### Cost-effectiveness analysis (CEA)

Direct costs per patient in PPEP4All versus the costs per patient in CAU are compared. The differences in mean costs and effects between strategies are compared with two-sided bootstrapping. In a net-benefit analysis, costs are related to patient-reported outcomes and presented in a cost-effectiveness acceptability curve (CEAC), which indicates the probability of PPEP4All being cost-effective. No discounting is applied considering the time horizon of 1 year. This economic evaluation is approached from a societal perspective and includes costs due to healthcare resource utilization (i.e., healthcare costs) and costs attributable to production losses [100]. Sensitivity analysis will test whether estimates are sensitive to plausible changes in perspectives (societal or healthcare perspective) and indirect costs (friction cost method and human capital approach). Furthermore, in an additional analysis, we extrapolate cost and effect estimates to a lifetime time horizon, in accordance with the recent Dutch directive for conducting economic evaluations in healthcare [101, 102]. In the base-case analysis, costs of absenteeism from paid work are calculated using the friction cost method, which estimates the indirect costs of disease, mainly occurring during the time it takes to replace a worker [103–106].

In this project, costs are calculated using standard unit prices published in the most recent Dutch Costing Manual [101, 102]. If references are not available, costs are estimated by cost research experts (i.e., LUMC Department of Medical Decision Making). The costs are divided into healthcare costs, costs of patients and partner/caregiver, and costs in other sectors (i.e., non-healthcare costs such as productivity costs). Healthcare costs include the costs of PPEP4All and other healthcare use during the first year of follow-up (e.g., GP visits, outpatient visits, hospital days, medication, home care, informal care). Costs of PPEP4All are based on micro-costing including time of caregivers and materials used. Costs of patients and partners/caregivers consist of time lost or productivity loss from paid/unpaid work of the patient, and time required for the PPEP4All meetings by partners/care givers.

#### Budget impact analysis (BIA)

In addition to the CEA, a BIA is performed according to the International Society for Pharmacoeconomics and Outcomes Research (ISPOR) Task Force principles [107, 108]. The BIA estimates the financial impact of implementation (i.e., adoption and diffusion) of PPEP4All in patients with PDD at the national level. The analysis is based on the costs estimated during the study and the expected number of patients eligible for this treatment in the Netherlands. Costs of the treatment and other consequences of it will be included in the BIA. The BIA is conducted from the perspective of the different healthcare payers (public purse or budgetary framework [in Dutch: Budgetair Kader Zorg (BKZ)]; health insurers; health care providers) and from the societal perspective (i.e., including productivity costs). If the PPEP4All intervention appears to be cost-effective in patients with PDD, the following scenarios will be compared: (a) intervention not yet implemented, (b) intervention implemented in 100% of the target group, (c) intervention gradually introduced over a period of 3 years. Sensitivity analysis is performed on the costs of the intervention and the diffusion rate. Factors that determine the budget impact are determined. Costs are estimated per budget period (1 year) for a time horizon of 3 years. In the societal perspective and healthcare perspective, standard prices will be used [101]. For the BKZ and health insurer’s perspective, tariffs established by the Dutch Healthcare Authority (Nederlandse Zorgautoriteit (NZA)) are used.

### Qualitative data

All patients and partners/caregivers who give consent to be approached for the nested follow-up qualitative study are invited by telephone to participate. The participant may choose where the in-depth semi-structured interview is planned: at the participant’s home, at the main research location (LUMC), or over telephone. Participants are compensated for travel and given a 20-euro gift card to thank them for their time. Participants are allowed to withdraw at any moment of the qualitative study.

For each interview, we use topic lists, or interview guides (see Supplementary Topic Lists in Additional Files 2 and 3), which were evaluated in a pilot study of patients with PDD and revised as necessary [109, 110]. The topics and questions are presented to the participant as they naturally arise during the interview, to maintain the flow of the interview. The qualitative study includes two parts that examined: (a) use of coping strategies of PDD patients and their partners/caregivers for chronic depression/suicidality and their specific needs for care; (b) satisfaction of patients, partners/caregivers, and therapists with PPEP4All (or CAU). The two parts are discussed in further detail below (see “Coping with chronic depression” and “Satisfaction”).

The interviews are recorded using a digital audio recorder and then transcribed by research assistants using the dictation feature of the online Transcribe application (https://transcribe.wreally.com). This application does not store documents; audio files are deleted after the window is closed, making it a secure method that maintains confidentiality after transcription work. Personal data that can be traced back to the participant (e.g., names of participant, family members, or employer) are removed, and transcripts are saved under a participant code. The verified transcripts are then checked and analyzed by the researcher (ES) and a research assistant. Each interview and the resulting themes are discussed with the research assistant and tracked using an audit trail, to provide systematic and detailed documentation of analytical decision making during the process. Memo writing is utilized throughout the analytic process. Discrepancies in coding are discussed until consensus on the data is established. Because we used a qualitative emergent approach focused on gaining new insights, rather than developing a theory, our analytical approach in this study can be described as using “Grounded Theory lite” [111–116]. For the analysis, using Atlas.ti version 9, transcripts are first coded line-by-line, then coded axially into emergent conceptual categories [113, 116, 117]. We also use constant comparison, a method in which we continuously compare the concepts or themes between data and emergent coded categories and the data of the interviews [117, 118]. The main goal of the study is greater conceptual clarity and to build a conceptual framework of the experiences of participants with chronic depression regarding their treatment needs and use of self-management to meet these needs [119].

### Coping with chronic depression

First, we aim to answer the following research questions: *how do individuals with chronic depression manage their chronic condition, and what are their experiences in relation to potential facilitators and barriers, personal strengths and hindrances, and use of self-management coping strategies?* (see Supplementary Topic List A, or Additional File 2, which is partly based on a previous relevant topic list [110]). For this part of the qualitative study, we predetermined the number of required participants to ensure a sufficient sample. According to guidelines, we aim to include between 25 and 40 patients from the PPEP4All or CAU groups and 15 PPEP4All partners/caregivers to reach saturation of the themes [120–122].

### Satisfaction

Second, we aim to evaluate satisfaction with PPEP4All and investigate how we can optimize it to meet the needs of the patients with PDD and their partners/caregivers. Our approach is multi-faceted: we conduct in-depth interviews with patients, partners/caregivers, and PPEP4All therapists (see Supplementary Topic List B, or Additional File 3, which is partly based on the Mental Healthcare Thermometer [109]), and we collect data using an evaluation questionnaire at the end of the fourth quantitative measurement to elucidate the positive and negative aspects of PPEP4All or CAU. During the interview, participants may provide feedback and suggestions regarding PPEP4All, and they rate the PPEP4All program on a scale from 1 to 10. We will provide the average rating for each group. This satisfaction rating reflects an indirect measurement of the effectiveness of PPEP4All. For this part of the qualitative study, we aim to include between 25 PPEP4All patients, 15 PPEP4All partners/caregivers, and 10 PPEP4All therapists [120–122]. In addition, we strive to measure satisfaction of participants of CAU. The procedure for evaluating CAU is the same as PPEP4All: we use an evaluation questionnaire and a qualitative interview. During the interview, participants can rate CAU on a scale from 1 to 10 and provide additional information regarding their experience with CAU, such as suggestions regarding what kind of treatment techniques they would prefer as CAU.

## Ethics, data management, and dissemination

The study protocol, informed consent forms, participant education, and recruitment materials were approved by the Medical Ethics Committee (MEC) of the LUMC. If there are any subsequent modifications to the protocol which may impact the conduct of the study, including changes of study objectives, patient population, sample sizes, study procedures, or significant administrative aspects, these will be submitted as an amendment and reviewed by the MEC of the LUMC for approval. The approved protocol modifications will be communicated to research locations and participants by email or newsletter. Subsequent to initial review and approval, the MEC will review the protocol annually and the researcher will make safety and progress reports to the MEC annually and within 3 months of study termination. These reports will include the total number of participants enrolled and any particularities that should be reported to the MEC. Due to the low risk associated with study participation, annual audit of the study, data monitoring committee, and interim analyses are not required. Additionally, a data safety monitoring board is not required because we do not investigate a medical product and we do not foresee any major risks associated with study participation or with participation in the intervention provided by trained therapists.

Written informed consent will be obtained from all participants prior to the baseline assessment. All informed consent forms will be arranged and co-signed by the researcher or trained research assistant who provided information regarding the study. For the nested qualitative study, each participant gave written consent to be approached for participation in this additional study. Participants thereafter gave verbal consent to the study including consent to audio recording and transcribe their interviews.

In general, we followed the guidelines for Good Research Practice (GRP) [123–126]. To protect the confidentiality of data and privacy of patients, we use a unique research code for each participant on all research-related participant forms, such as contact forms or paper questionnaires. This enables the research team to identify individuals without using names. The list linking the participant code to personal information is kept in a secure electronic database with access limited to the designated researcher (ES) and independent data coordinator (GC). The list may be assessed and the main mental health clinician of the patient informed, if required for the sake of the safety of the participant. All electronic research-related participant information is stored on a protected network in a secure file with limited access. The hardcopy paper research information is kept in a locked cabinet in a secure area of the LUMC department. Any documents with information traceable to the participant are kept in locked files separate from the patient data with limited access. To uphold high standards of research, all researchers, research coordinators, and research assistants successfully completed the research certification for Good Research Practice (GRP). Additionally, all research team members completed a training workshop regarding the trial procedures and questionnaires, use of QuestManager, and administration of the MINI screening interview.

Moreover, after the data analysis phase, patient privacy will be further maintained. The results obtained from the questionnaires will be described on a group level to prevent the data being traced back to a single person. Data will be kept on the secure network for maximum 3 months at the end of the research project as the embargo period, for the sole purpose of completing data analysis, as per the policy of the funding sponsor. Once the final report of the study is available, the study results will be extensively disseminated to the international scientific community in the form of peer-reviewed journal articles, giving preference to open-access journals.

After the embargo period, the pseudonymized data will be stored for 15 years on an online Dutch meta-data catalogue called the Data Archiving and Networked Services (DANS, www.dans.knaw.nl) together with a data dictionary, as is common practice for mental healthcare research in the Netherlands. Only the designated researchers will have access to the final data set. External researchers may get access to the final trial dataset from the designated team on reasonable request.

## Discussion

### Scientific and clinical importance of this study

The present study examines the clinical- and cost-effectiveness of a brief self-management intervention, namely PPEP4All, in patients with PDD and their partners/caregivers. Although self-management is more common in the treatment of somatic illnesses, it is gaining popularity in mental healthcare. Psychiatric rehabilitation via self-management is the next step in the revised international multidisciplinary treatment guidelines for chronic depression after psychotherapy and pharmacotherapy have been attempted with inadequate results. In this context, there is an urgent need in mental healthcare for a brief specific self-management protocol that could replace the long-term non-specific care for patients with PDD (care as usual).

### Study implications

The findings of this study will have potential implications for the implementation of self-management on a national level in the Netherlands and could be further incorporated into the multidisciplinary treatment guidelines for depression. The Netherlands has recently seen a shift in the mental healthcare system due to tighter healthcare budgets. Mental healthcare clinics are looking for empirically supported protocolized treatments that can reduce healthcare costs. With this in mind, PPEP4All is a brief self-management intervention that can be provided when depression treatment leads to unsatisfactory reduction of symptoms, typically after a 2-year treatment period. The expectation is that empowering patients via PPEP4All will decrease the number of ongoing supportive sessions of CAU, for which there is currently little to no empirical evidence [13].

The present study has several strengths. First, in line with the pragmatic nature of the project, we focus on external validity: we evaluate the standard care (CAU) already provided by healthcare professionals in multiple mental healthcare clinics. Moreover, the broad inclusion criteria allow the recruitment of patients with a wide range of comorbidity, as typically seen among persons with chronic or recurrent depression. We expect the resulting sample to be broadly representative of outpatients and generalizable to the population of persons with chronic depression. We selected only the most crucial research questionnaires to limit the burden on the patients; therefore, we expect limited effect of the test battery on patient drop-out. Additionally, by using a mixed methods research approach, we are able to evaluate both quantitative and qualitative aspects of PPEP4All from multiple perspectives (patient, partner/caregiver, clinician).

### Challenges concerning trial recruitment and implementation

We wish to report some early challenges we faced in the recruitment of participants and implementation of our study design and PPEP4All in the participating research centers. After all, patient recruitment is a key determinant of success or failure for clinical trials [127–129].

Firstly, we learned that recruiting only patients with a primary diagnosis of chronic depression/PDD limited our ability to also recruit potential participants with secondary, or comorbid, PDD (e.g., bipolar disorder type II participants with comorbid PDD). After careful deliberation, we allowed these participants to enroll in our study considering that PPEP4All is a generic self-management program that could potentially be used for a wide range of psychiatric disorders and its focus is on recovery, stabilization, and reintegration into the community [130].

Secondly, we had to make the following adjustments to reduce participant drop-out [93]. Initially, we had proposed providing PPEP4All as group treatment, because a group could be the most cost-effective and efficient modality for mental healthcare. However, several patients with PDD preferred individual PPEP4All and therefore refused to participate. This possible preference for individual PPEP4All was also reported to us by the Client Council of the participating centers. For this reason, although PPEP4All is still primarily offered as a group treatment, we also allow the option to provide PPEP4All as an individual treatment (same protocol). In addition, for patients with a preference for group PPEP4All, we lowered the minimum threshold of required group participants to three rather than the original five, which allowed us to start PPEP4All groups without a long waiting period. Moreover, some patients who explicitly wanted PPEP4All withdrew their study participation after they were randomized to CAU. We remedied this with the message that, if necessary, these patients could receive PPEP4All after CAU and completing at least their first or second follow-up.

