**Fig. 3 Fig3:**
[figure not shown]
An overview of the self-management themes of the PPEP4All sessions for the patient and the partner/caregiver. *Notes:* PPEP4All = Patient and Partner Education Program for All Chronic Illnesses. Patient and partner/caregiver programs include the same themes with the exception of sessions 5 and 8. Each session has a general structure of discussing previous homework, presenting active information (i.e., the theme), performing an active exercise, then providing homework and a preview of the next session. The trainer is the PPEP4All therapist. ^a^Participants also gain insight by using a body awareness exercise. ^b^In partner/caregiver program, session 5 focuses on caregiver burden and stress (overload) and relevant challenges. ^c^In partner/caregiver program, session 8 focuses on making a self-care plan

The partner/caregiver program (separate partner group) is the same as the patient program with only one difference: session five focuses on dealing with caregiver burden and patient suicidality (see Fig. 3). The patient and partner/caregiver receive PPEP4All workbooks with homework assignments after each session to practice skills and integrate information. Although the original protocol describes a minimum of 5 and a maximum of 10 participants per group [17], we allowed groups to start with as few as 3–4 participants to avoid undue waiting times.

The PPEP4All program is eclectic, including theoretical influences of system theory (“patient system”) [68, 69], cognitive behavioral theory (“(dys) functional cognitions”) [70], social cognitive theory (“self-efficacy”) [71], stress-coping model (“coping strategies”) [72, 73], transtheoretical model (“motivation to change”) [74]; bio-psycho-social model (quality of life) [75–77], and generic model of self-management [78].

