## Sample size and power calculation

We based our sample size on the effect size of previously conducted randomized controlled trials that evaluated relevant interventions in a similar setting in patients with chronic or treatment-resistant depression and that reported a quality of life outcome measure [83, 84, 88–90]. We can expect an effect size around 0.35 [90]. Considering a power level of 80%, alpha of 95%, and equal allocation ratio, we would require 81 participants per group [91–95]. With an additional 16 persons to account for an expected attrition of 10% [96], we expect to include a total sample of 178 participants (2 × 89).

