### Clinical effectiveness

The mean quality-adjusted life years (QALYs) are estimated using EQ-5D-5L data from four assessments. For the *primary data analysis*, we perform an analysis of covariance for the QALY’s using the post-test EQ-5D-5L results with the pre-test scores as covariate [92–94]. In this way, we test whether there is a difference between PPEP4All and CAU, accounting for the variation where the patients started at the first measurement. For the *secondary data analyses*, secondary parameters are tested using weighted generalized estimating equation (GEE) analyses [97, 98]. Clinical effectiveness analyses are examined using superiority testing.

Moreover, we examine tailored care by further investigating for which groups PPEP4All is the most effective. If possible, subgroup analyses are performed for age, gender, ethnicity, and intervention modality (group/individual). In this context, we explore relevant socio-demographics (e.g., education, living situation, and work) and clinical variables (e.g., comorbidity, baseline severity of disease).

For all outcome analyses, an intention-to-treat (ITT) approach is used, according to the CONSORT statement [99]. Analyses are conducted in SPSS, Stata or R.

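### PPEP4All is given mainly in therapy groups and CAU mostly individually, but neither the sample size nor the named primary ANCOVA allows for correlation within groups

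*Protocol article*

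**What the plan says.** **Delivery.** The section on recruitment challenges reports that an individual option was added, "although PPEP4All is still primarily offered as a group treatment". The section on the self-management intervention gives the programme's usual group size as "a minimum of 5 and a maximum of 10 participants per group", then says that groups in this trial may start with three or four. The section on care as usual describes a mostly individual treatment. Randomisation is of individual patients, stratified by gender and research center.

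**Sample size.** The inputs are an effect size ("We can expect an effect size around 0.35"), power, alpha and allocation ("Considering a power level of 80%, alpha of 95%, and equal allocation ratio, we would require 81 participants per group"), and attrition ("an additional 16 persons to account for an expected attrition of 10" per cent), giving 178 in total. No ICC, group size or design effect appears.

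**Analysis.** The primary analysis is an ANCOVA "using the post-test EQ-5D-5L results with the pre-test scores as covariate". No term for therapy group is named. Weighted GEE is reserved for secondary parameters, and modality (group or individual) appears only as a possible subgroup factor. On the economic side, "The differences in mean costs and effects between strategies are compared with two-sided bootstrapping", with no resampling unit given.

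**The concern.** Patients in one therapy group share nine sessions, a therapist and each other's company, so their outcomes may be more alike than those of patients from different groups. Individual randomisation does not remove this, because the correlation arises after allocation. The PPEP4All mean then carries less information than its patient count suggests, while the CAU mean is largely unaffected. An ANCOVA that treats every patient as an independent observation takes the residual variance at face value and understates the standard error of the treatment difference.

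At stake are the nominal 5% level of the primary superiority test, the width of its confidence interval, and the power claimed for 178 patients. The same QALY data feed the cost-effectiveness analysis. An error that ignores clustering there would make the acceptability curve too precise.

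**Working it through.** **1. The plan's own figure.** I read the printed alpha of 95% as 0.05 and the effect size as a standardised mean difference. The clinical test is described only by "Clinical effectiveness analyses are examined using superiority testing", so I assume it is two-sided.

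- Two-sided, no covariate: n per arm = 2 × (1.960 + 0.842)² / 0.35² = 128.1, so 129. One-sided gives 101. Neither is 81.
- An ANCOVA multiplies n by (1 − ρ²), where ρ is the correlation of baseline with outcome. To reach 81 needs ρ = √(1 − 81/128.1) ≈ 0.61 two-sided, or about 0.44 one-sided. The article states no ρ.
- Total: 2 × 81 + 16 = 178. Dividing 162 by 0.9 gives 180, which is close.

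The printed inputs therefore do not reproduce 81, and none of them is an allowance for clustering. Below, 80% power at 81 per arm is taken as the plan's nominal claim, not as something confirmed.

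**2. Effect of clustering in one arm.** Let m be the number of trial patients per therapy group, s the share of PPEP4All patients treated in groups, and ICC the within-group correlation of outcomes after baseline adjustment.

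- Design effect, PPEP4All arm: DE = 1 + s(m − 1)ICC; CAU arm: 1.
- True variance over model variance of the difference, equal arms: V = (1 + DE)/2.
- Actual two-sided alpha = 2 × [1 − Φ(1.960/√V)].
- Power with a correct standard error = Φ(2.802/√V − 1.960).

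The values of ICC and s are assumptions; the range of m comes from the article. Worked case with ICC 0.05, m = 5, s = 1: DE = 1 + 4 × 0.05 = 1.20; V = 1.10; √V = 1.049; alpha = 6.2%; power = 76.2%.

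| ICC | m | s | √V | alpha | power |
|---|---|---|---|---|---|
| 0.01 | 3 | 1 | 1.005 | 5.1% | 79.6% |
| 0.01 | 5 | 1 | 1.010 | 5.2% | 79.2% |
| 0.05 | 3 | 1 | 1.025 | 5.6% | 78.1% |
| 0.05 | 5 | 1 | 1.049 | 6.2% | 76.2% |
| 0.05 | 5 | 0.6 | 1.030 | 5.7% | 77.7% |
| 0.05 | 10 | 1 | 1.107 | 7.7% | 71.6% |
| 0.10 | 3 | 1 | 1.049 | 6.2% | 76.2% |
| 0.10 | 5 | 1 | 1.095 | 7.4% | 72.5% |
| 0.10 | 10 | 1 | 1.204 | 10.4% | 64.3% |

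**3. Check by simulation.** The plain ANCOVA was simulated with 81 per arm, ρ = 0.6, s = 1 and 10,000 runs per setting. Rejection under no effect was 5.0% at ICC 0. At ICC 0.05 it was 5.6% (m = 3), 6.0% (m = 5), 6.4% (m = 7) and 7.5% (m = 10). This agrees with the formula.

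**4. Which rows are plausible.** The article gives 89 patients per arm, 11 locations and recruitment from April 2017 to April 2021. That is 89/11 ≈ 8 PPEP4All patients per location over four years. Groups of eight to ten trial patients would take about a location's whole intake at once, whereas the article reports lowering the minimum to three to avoid waiting. Groups of 3 to 5 are the more realistic setting.

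**The case against.** The strongest objection is that this is silence, not error. A journal article gives the primary model in a sentence, and the random-effect structure, degrees of freedom and bootstrap unit usually sit in a SAP. The ANCOVA sentence does not say that a group term is excluded. That stands for the bootstrap: a reader might infer that it ignores groups, but no resampling unit is named, so this can only be a request to specify one. It does not dispose of the rest. The sample-size inputs are printed in full without a clustering allowance, and the model as named, if followed, ignores the groups.

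Second, the size is easily overstated. A reader might infer that type I error definitely exceeds 5%, or reaches about 9% with power near 67% (the result for m = 8 and ICC 0.10: DE = 1.70, V = 1.35). The documents support neither. They give no ICC and no share treated in groups, and groups that large are unlikely given the intake per location. Individual delivery dilutes the effect. Leaving the stratification factors out of the ANCOVA is slightly conservative and could offset a very small ICC.

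Third, shared therapists add little to the argument. There are 34 for 89 PPEP4All patients, about 2.6 each, and CAU patients also have their own therapists, so therapist clustering is not peculiar to one arm.

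Fourth, a reader might infer that the acceptability curve would flatter PPEP4All. Understated variance makes the curve too extreme in either direction; it raises the probability only where that already exceeds one half.

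**Conclusion.** The point holds as a conditional one. Group delivery in one arm makes the trial partially nested; the printed sample size makes no allowance for it, and the primary model as named does not either. For any positive within-group correlation the clustering makes the ANCOVA standard error too small.

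Under the central assumptions (ICC 0.05, groups of 3 to 5, everyone in groups) the standard error is 2.5% to 5% too small relative to the truth, and the excess in type I error is about 0.6 to 1.2 percentage points. The power loss is 2 to 4 points from a nominal 80% that the printed inputs do not themselves yield. At ICC 0.01 in such groups the effect is negligible. It becomes material only with bigger groups or an ICC near 0.10. Severity: should fix.

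**What to change.** - **Primary analysis.** Use a partially nested mixed model: the baseline-adjusted comparison with a random effect for therapy group in the PPEP4All arm, individually treated and CAU patients as singletons, arm-specific residual variance and small-sample degrees of freedom.
- **Data.** Record each patient's therapy group alongside the attendance lists described under treatment integrity. The article says that attendance is recorded, not that group membership is.
- **Cost-effectiveness analysis.** State that the bootstrap resamples therapy groups as clusters in the PPEP4All arm, with individually treated and CAU patients resampled singly.
- **Power.** Restate the power at 178 over a declared range of ICC and group size, with the baseline correlation it relies on. Do not enlarge the trial.

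The cost is some wording, one model term and one recorded variable. Intervals will be slightly wider and the stated power slightly lower. Recruitment was still open at protocol Version 7, so the change can be made before analysis.
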